## Abstract

**Introduction:**

In the UK, a compulsory ‘6-week hip check’ is performed in primary care for the detection of developmental dysplasia of the hip (DDH). However, missed diagnoses and infants incorrectly labelled with DDH remain a problem, potentially leading to adverse consequences for infants, their families and the National Health Service. National policy states that infants should be referred to hospital if the 6-week check suggests DDH, though there is no available tool to aid examination or offer guidelines for referral. We developed standardised diagnostic criteria for DDH, based on international Delphi consensus, and a 9-item checklist that has the potential to enable non-experts to diagnose DDH in a manner approaching that of experts.

**Methods and analysis:**

We will conduct a controlled trial randomised by practice that will compare a diagnostic aid against standard care for the hip check. The primary objective is to determine whether an aid to the diagnosis of DDH reduces the number of clinically insignificant referrals from primary care to hospital and the number of late diagnosed DDH. The trial will include a qualitative process evaluation, an assessment of professional behavioural change and a full health economic evaluation. We will recruit 152 general practitioner practices in England. These will be randomised to conduct the hip checks with use of the study diagnostic aid and/or as per usual practice. The total number of infants seen during a 15-month recruitment period will be 110 per practice. Two years after the 6-week hip check, we will measure the number of referred infants that are (1) clinically insignificant for DDH and (2) those that constitute appropriate referrals.

**Ethics and dissemination:**

This study has approval from the Health Research Authority (16/1/2020) and the Confidentiality Advisory Group (18/2/2020). Results will be published in peer-reviewed academic journals, disseminated to patient organisations and the media.

**Trial registration number:**

NCT04101903; Pre-results.

Strengths and limitations of this studyTo our knowledge, this is the first trial to evaluate a diagnostic aid for the 6-week check with reference to evaluating both missed and unnecessary referrals to hospital.Implementable on existing clinical software used by general practitioners, the proposed aid will be easy to use.A comprehensive process evaluation, using qualitative methods and behavioural change frameworks, will be done alongside to the trial; plus a full health economic evaluation.The reliance on existing practice staff to report monthly updates is essential but could pose a risk to timely and complete data collection.The collection of identifiable data through site visits across 152 practices will be challenging.

## Introduction

Developmental dysplasia of the hip (DDH) is characterised by varying displacement of the proximal femur from the acetabulum with associated acetabular dysplasia. Dislocation occurs in 1–2/1000 infants per year but milder forms occur in 40–60/1000.^1^ Early recognition of disease is associated with better outcomes. It is national policy^2^ to examine all infants for the presence of DDH at birth and at age 6–8 weeks in primary care (6-week hip check). If diagnosed within the first 6–8 weeks, splinting of the hips is successful in 85% of cases.^3^ Later diagnoses usually will require invasive treatment, with many years of continued monitoring.^4^ Late diagnosed DDH is a common cause of medical negligence claims, with increased suffering for affected patients.

Timely diagnoses of DDH remain a challenge despite the compulsory 6-week check.^5^ In one study, the median age at diagnosis was 14 months, with only 40% of infants diagnosed during routine examinations and 60% presenting owing to parental concerns.^6^ In another study, 30% of infants were not diagnosed by 12 weeks.^7^ Because there is no further compulsory check after that at 6 weeks, it is vital that the 6-week check is effective. Also infants incorrectly identified with ‘DDH’ in primary care and referred to hospital remain a challenge for both families and National Health Service (NHS). This group does not require treatment and reassurance provided in primary care would avoid unnecessary anxiety and inefficient use of hospital resources. Of 1918 infants referred to hospital from primary care for DDH, only 64 (3%) had DDH^7^ but 1270 (66%) were identified as ‘DDH’ based on inappropriate criteria,^8^ for example, ‘crease asymmetry’ (n=234) or ‘click’ (n=648). If general practitioners (GPs) were able to discriminate better between benign abnormalities requiring reassurance (perhaps with a follow-up in primary care) and findings requiring referrals, outcomes of infants with and without DDH would improve.

In prior research we suggested that too many diagnostic criteria^8^ and variability in the use of diagnostic criteria among clinicians^9^ complicate the task of diagnosing DDH. We developed standardised diagnostic criteria to reduce the variability in assessment and management decisions in infants examined for DDH.^10^ The weighted criteria demonstrated validity.^10^ In a study of 44 patients referred from GPs to hospital, the weighted criteria demonstrated a positive predictive value of 89% (95% CI 70% to 97%) and negative predictive value of 76% (95% CI 50% to 96%).^11^ We refined these binary criteria, in form of a checklist with nine items, for use by GPs during the 6-week hip check and developed a training video, featuring a GP. This checklist and video were refined in a feasibility study which used qualitative methods to explore the acceptability of the format, style and delivery of the intervention (report available on request). The video explains the meaning of the diagnostic criteria; it also demonstrates how precisely to elicit the diagnostic criteria. For example, the video explains the difference between the Barlow and Ortolani manoeuvres, how to test for a leg length inequality or how to identify limitations in hip abduction.

### Rationale

Current referral patterns suggest there could be considerable health gains from improved diagnostic and referral decisions at the 6-week check.^5^ GPs, in a preparatory focus group, identified the need for a ‘comprehensive, structured guide’ for the 6-week check. Diagnostic aids enable physicians to overcome barriers in diagnostic reasoning^12^ by shifting intuitive to analytical aspects of diagnostic reasoning. Decisions made under these circumstances approach normative reasoning and rationality more closely, and are more reliable and safer.^13^ Building on our earlier research, we propose to facilitate GP’s diagnostic reasoning at the 6-week check by structuring current practice with use of a previously developed diagnostic aid. A diagnostic aid of this kind provides a structured approach to the assessment of infants and offers guidance about referrals.

### Objectives

To determine whether an aid to the diagnosis of DDH reduces the number of clinically insignificant referrals from primary care to hospital, and the number of late diagnosed DDH.To determine the cost-effectiveness of this intervention.To conduct an integrated qualitative and quantitative process evaluation in order to understand all participants’ experience in the trial and with the intervention; study how the intervention is implemented; investigate contextual factors that affect the intervention.

## Methods and analysis

The Standard Protocol Items: Recommendations for Interventional Trials reporting guidelines were used in the preparation of this clinical trial protocol.^14^

### Design

This is a cluster randomised controlled trial of GP practices in England, with randomisation and intervention at practice level but the primary endpoint measured at patient level (figure 1). An internal pilot will be done in the first 4 months to ascertain accrual rates—we will progress to the main trial if we succeed in recruiting ≥12 practices per month (expected recruitment is ≥21 practices/month for the main trial). Incorporated in the trial are (1) a process evaluation investigating determinants of GPs’ referral behaviour and the implementation of the intervention in practice and (2) a health economic evaluation in a child’s lifetime.

**Figure 1 F1:**
[figure not shown]
Flow chart demonstrating pathways and principal endpoints and their collection. DDH, developmental dysplasia of the hip; GP, general practitioner; HES, Health Episodes Statistic.

### Eligibility and recruitment

GP practices registered in England that carry out 6-week hip checks (at age 42–76 days) and agree (1) to being randomised and (2) to hospitals releasing data concerning infants they examine in the trial. Ineligible are practices planning to close with 12 months of trial start.

We anticipate that ≥110 infants per year will undergo the 6-week hip check in each of the recruited practices. Each practice will recruit infants for a period of 15 months and infants will be followed for 2 years. This trial is planned therefore to run for 44 months across 152 GP practices.

### Retention

The proposed trial is not onerous on the practice staff and practices will not be challenged by excessive study-related manoeuvres. Because the primary outcome will be collected using practice and hospital databases only, it is likely that we will attain high levels of follow-up. We will send periodic newsletters to GPs and foster regular contacts.

#### Randomisation

Practices will submit an eligibility form to the clinical trials unit, which will register and randomly allocate (concealed) practices within 48 hours. An independent statistician will coordinate randomisation with an allocation ratio of 1:1 and stratified by practice size (based on observed sizes obtained from expressions of interest—we expect two or three strata).

### Interventions

#### Control intervention

GPs will assess infant hips following best practice principles; they will be provide a leaflet about the national best practice recommendations.^2^

#### Experimental intervention

This is a complex intervention comprising a video developed specifically for this trial and a diagnostic aid in form of a 9-item binary checklist. At the time when informed consent is taken, GPs will watch the video. They will then examine all infants in the 6-week check according to best practice principles, but with the addition of the diagnostic aid (implemented electronically to each practice’s computer system).

According to national guidelines, the 6-week check shall capture infants at age 6–10 weeks and infants in whom a diagnosis of DDH is considered should see a specialist within 2 weeks.^2^ Participating GPs of both intervention arms will be asked to adhere to this policy.

### Definitions for the purpose of this trial

‘Appropriate referral’ denotes a referred hip deemed 'clinically significant', that is, is treated or monitored (at least one follow-up) by a specialist surgeon. Any ambiguous cases will be reviewed by our expert advisory panel who will assign an ultimate diagnosis in consensus. ‘Clinically insignificant’ are referred hips resulting in reassurance and discharge from surgeons’ clinics (ie, no treatment or monitoring). ‘Late diagnoses’ are cases of DDH diagnosed by a specialist surgeon at age 3–24 months.^15 16^

### Sample size calculation

We based its calculation on Poisson regression and audit data from the Nottingham area (partially presented in Price *et al*^7^) and University College Hospital (audit of 3 years’ practice, unpublished data): a conservative estimate of the number of infants referred as a consequence of the 6-week check within the recruitment period of 1 year is, on average, 3 per practice. Based on the same data, we estimate that about one in three (or, on average, one per practice) of such referrals is correctly made (‘appropriate’ referrals, defined above as ‘clinically significant’, are a subset of these ‘correct’ referrals). Thus, on average, we expect 2 ‘incorrect’ referrals per practice. These are the ones we seek to reduce, and the intervention should serve to cut them by 50%. Thus we aim to detect a reduction, on average, from 3 to 2 referrals per practice in the intervention arm. To account for correlation within practices, which can also be thought of as overdispersion relative to the underlying Poisson variation, we assumed a between-practice component of variance of 20% of the average Poisson ‘counting’ variance per practice. For 90% statistical power and testing two sided at p=0.05, we need 76 practices per group (15% of this total comprises a safety margin to allow for potential challenges). Average referral rates from the Nottingham (2.8%) and University College Hospital data (2.7%) are very consistent, and suggest a target of about 110 children per practice per year to undergo the 6-week check.

### Primary trial endpoint

Number of referred infants that are considered ‘clinically insignificant’—this is a measure of the clinical importance of referrals in the 2-week hip pathway. We chose this outcome because it is extremely relevant clinically and one for which it is possible to power the trial.^2^ An intervention could be successful at achieving this outcome while missing infants who do have DDH; we thus specified a principal secondary endpoint. False negatives are also important but, because of their rarity, would not be an efficient endpoint on which to power the trial (and would thus be outside International Council for Harmonisation of Technical Requirements for Registration of Pharmaceuticals for Human Use (ICH) E9),^17^ which recommends that the primary outcome should be both clinically and statistically convincing). A research assistant will retrieve these data from respective hospital electronic systems by conducting site visits to all secondary care facilities to which GPs refer infants, starting 6 weeks after the last patient enters the trial.

### Secondary trial endpoints

#### Infant level

Number of appropriate referrals per practice (principal secondary endpoint): for all infants referred as a consequence of the 6-week check, a researcher will collect, using unique NHS patient numbers, and categorise the appropriateness of referrals by a practice with respective hospital databases using a standardised taxonomy, blind to practice random allocation. She/he will conduct site visits to all such hospitals starting 6 weeks after the last patient entered the trial.Number of late diagnoses: We will employ deterministic methods of data linkage. Using unique NHS numbers of any recruited infant, we will obtain from Health and Social Care Information Centre the corresponding Health Episodes Statistic (HES) identifiers. HES is a data warehouse that includes all hospital admissions and outpatients’ visits occurring in all hospitals in England. In HES, we will establish whether any infant in the trial was admitted to a UK hospital as a result of DDH using relevant International Statistical Classification of Diseases and Related Health Problems (ICD)-10 codes and Office of Population Censuses and Surveys (OPCS)-4 codes.^18^ We will extract, for the whole trial period, the full hospital history for all infants in the trial (in and out patient episodes), collate all episodes into a combined exploratory analysis view, collate interactions, and allocate outcomes to practice groups to facilitate outcome analyses.^19^ These data will be compared with the data collected by the researcher (see above); the use of these two strategies will enhance the robustness of data.Consequences of late diagnoses: Using data collected above we will record nature and frequency of such consequences (nature of treatment, length of hospital stay, frequency of secondary care contacts).Health-related quality of life (parental proxy report): Child-Health-Utility-9D.^20^

#### Process level

Volume of referrals: Total number of patients referred to secondary care during the trial period. This variable will be collected prospectively at practice level by the participating GP and forwarded monthly to the clinical trial unit.Timeliness of referrals: In infants referred to secondary care, we will measure the days from referral issued to hospital appointment (collected in the same way as primary endpoint). This process measure will inform about target wait times^2^ achieved.

#### Clinician level

Confidence and attitudes of GP and secondary care clinicians towards the diagnostic aid: will be assessed 12 weeks after trial set-up and at trial completion using a modified measure based on the theory of planned behaviour.^21^Implementation issues and acceptability of diagnostic aid among GPs and secondary care providers: we will conduct qualitative research at the trial end to elicit this information.Use of diagnostic aid and acceptability of intervention: a self-administered questionnaire to evaluate the use of the aid will be posted to all the GPs in the intervention group; also direct observations and interviews will ascertain this outcome.

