#### Parent/carer level (collected from one in ten parents/carers)

General worry: State-Trait Anxiety Inventory 6-items short form.^22^DDH-related worry: Infant Hip Worries Inventory.^23^Satisfaction with trial: dimensions of care items from EUROPEP^24^ (table 1).

**Table 1 T1:** Assessments at different time points

	Baseline	At 6 week hip check	Within 2 weeks of intervention	3 month follow-up	15 month follow-up	2 year follow-up
Clinician-level						
Theoretical Domains Framework questionnaire	X		X	X	X	X
GP characteristics questionnaire	X					
Fidelity questionnaire			X	X	X	X
Non-participant observations		X				
Semi-structured interviews			X		X	
Parent/carer-level						
State Trait Anxiety Inventory six item short form			X			
Infant Hip Worries Inventory			X			
EUROPEP			X			
Non-participant observations		X				
Semi-structured interviews			X			
Out-of-pocket-costs questionnaire			X			
EuroQol 5 Dimension Scale (EQ-5D)			X			X
Child Health Utility 9D (CHU 9D)						X
Willingness-to-pay questionnaire					X	

GP, general practitioner.

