#### Quantitative outcome measures

We will summarise scores by instrument, accounting for practices and report difference in group means for each treatment arm. We expect mean scores to be lower in the intervention arm for State-Trait Anxiety Inventory and Infant Hip Worries Inventory, but higher or equal for EUROPEP.

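### The clinician attitude endpoint has one instrument and two assessment times in the text, but a different instrument and five times, including a baseline, in Table 1

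*Protocol article*

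**What the plan says.** Under the clinician-level secondary endpoints, the Protocol article names the outcome as "Confidence and attitudes of GP and secondary care clinicians towards the diagnostic aid". It is to be measured "using a modified measure based on the theory of planned behaviour", and it "will be assessed 12 weeks after trial set-up and at trial completion". That makes two times, neither of them a baseline.

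Table 1, headed "Assessments at different time points", has a block of clinician-level rows. None refers to the theory of planned behaviour. The row nearest in kind is the "Theoretical Domains Framework questionnaire", marked at baseline, within 2 weeks of the intervention, and at 3 months, 15 months and 2 years. Only the column for the 6-week check is blank.

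For questionnaire scores, the section on quantitative outcome measures says: "We will summarise scores by instrument, accounting for practices and report difference in group means for each treatment arm". The expected directions that follow concern parent and carer scales only ("We expect mean scores to be lower in the intervention arm for State-Trait Anxiety Inventory and Infant Hip Worries Inventory", then EUROPEP). No clinician scale and no baseline value is mentioned there.

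**The concern.** A secondary endpoint is fixed by what is measured, with which instrument, and when. Here the article gives the instrument and the schedule twice, and the two statements differ. Someone checking the final report against the protocol could not tell which questionnaire, or which of up to five times, was the planned outcome. That leaves room to choose an instrument or time point after the scores are known.

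The process evaluation is one of the trial's stated objectives, and its section says that clinician outcomes will be collected from all 152 sites. What is collected from clinicians, and when, is a matter for the protocol. An analysis plan written later cannot recover a baseline that was not taken, and on the schedule in the text none would be. If the baseline in Table 1 is taken, the text says nothing about what it is for.

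**Working it through.** The main check sets the two places side by side.

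| Item | Text, clinician-level endpoints | Table 1, clinician-level rows |
|---|---|---|
| Instrument | Modified theory-of-planned-behaviour measure | Theoretical Domains Framework questionnaire |
| Baseline | No | Yes |
| Within 2 weeks of the intervention | No | Yes |
| 12 weeks / 3 months | Yes | Yes |
| 15 months | Only if this is trial completion | Yes |
| 2 years | Only if this is trial completion | Yes |
| Number of times | 2 | 5 |

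*Instrument.* The Theoretical Domains Framework is not named anywhere in the article's text, and the theory of planned behaviour is not named anywhere in Table 1. If one instrument is meant, one of the two labels is wrong. If two are meant, the endpoint's own measure is missing from the assessment table, and the questionnaire in the table is tied to no named endpoint. Either way the two places need reconciling.

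*Timing.* Twelve weeks and 3 months can be taken as the same visit. Trial completion could be the 15-month column, because the eligibility section gives each practice a 15-month recruitment period, or the 2-year column, because infants are followed for 2 years. So at most 2 of the 5 times in the table appear in the text. Baseline, the 2-week assessment and one of the two late times appear in the table alone.

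*What a baseline covariate could be worth.* The article gives no correlation between baseline and follow-up scores, so r = 0.5 and r = 0.7 are assumptions. For independent subjects, adjusting for baseline multiplies the variance of the arm difference by 1 − r²:

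- r = 0.5: 1 − 0.25 = 0.75, a reduction of 25%.
- r = 0.7: 1 − 0.49 = 0.51, a reduction of 49%.

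The formula ignores clustering. If several GPs answer in each practice, the gain depends on the correlations at both practice and GP level, so these figures are illustrations and not estimates for this trial.

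**The case against.** The strongest reply is that these may be two instruments. The text endpoint concerns attitudes to the aid, in secondary care clinicians as well as GPs. The Theoretical Domains Framework questionnaire may belong to the separate assessment of professional behavioural change announced in the abstract. The article never equates the two. This stands in part: a reader might infer that the two schedules cannot both be followed, and the document does not support that, because two questionnaires could run side by side. It does not remove the mismatch, since each would then be missing from the other place. Nor does condensation for a journal explain it. Condensing accounts for omissions, but not for two differing statements.

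A second reply concerns the baseline. A reader might infer that it will go unused. The article does not say so. Adjusting a secondary questionnaire for baseline is commonly left to the full protocol or the analysis plan, neither of which is shown. The analysis section does account for practices, and it names only parent scales, so it is not certain that it governs the clinician questionnaire at all. This stands. What can be said is that the text gives the baseline no role.

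A reader might also infer that, without baseline adjustment, earlier differences between GPs would bias the comparison. Practices are randomised 1:1 with 76 per group, so such differences are balanced in expectation. Only precision is at stake.

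Finally, attitudes to an aid that GPs have not yet received are hard to score at baseline, and secondary care clinicians are not randomised. This stands too, and it limits where a baseline-adjusted comparison between arms makes sense.

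**Conclusion.** The point holds as a contradiction within the article about one secondary endpoint: different instrument names, two assessment times against five, and no baseline against a baseline. It does not depend on whether one instrument or two is meant.

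It is minor. The primary endpoint, the sample size and the type I error are untouched. The possible precision gain, a 25% to 49% lower variance, rests on assumed correlations of 0.5 to 0.7 and on independent subjects. It applies only to a comparison between arms of the randomised GPs' scores on a questionnaire for which a baseline exists.

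**What to change.** Reconcile the clinician-level endpoint text with Table 1. State:

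1. whether there is one instrument or two, named identically in both places, and, if two, which endpoint each serves;
2. which of the listed times define the endpoint and which are descriptive;
3. whether trial completion means the 15-month or the 2-year assessment;
4. what the baseline in Table 1 is for.

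Where the randomised GPs' questionnaire is compared between arms, keep the stated accounting for practices and add the GP's baseline score as a covariate. Report secondary care clinicians separately, because they were not randomised. The choice among the scheduled times is the sponsor's, but it should be written down before the scores are seen.

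The cost is a few sentences of wording and one term in a model. Table 1 already schedules the baseline for its questionnaire, so no extra assessment is needed if that instrument is kept. If the theory-of-planned-behaviour measure is a separate instrument, it needs its own row in the table.
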